#### Intervention Group (Group II)

Patients belonging to the intervention group are treated according to a modified aftercare protocol. We recommend shower irrigation for the nonsterile treatment twice a day. The patient is recommended to use a shower with room temperature water and irrigate the entire wound cavity with gentle pressure for 1 to 2 minutes using water only. The use of shower gel, soap, or shampoo is forbidden. After wound irrigation, the dressing of the wound with a moist and unfolded gauze followed by a dry nonsterile gauze and tape is carried out similar to the control group.

The first postoperative wound dressing is changed by the nurse and surgeon on the ward. The patient and/or family members are trained to adequately manage the wound and change the dressings. In case the patient is unable to change the dressing alone, the same home-care service is requested to support the patient. The home-care service is informed with a standard form.

### Outcome

As we present a noninferiority approach, the purpose of this analysis is to show comparable results in the intervention group in terms of reinfection and reoperation rates.

#### Primary Outcome

We defined the primary endpoint as a reinfection or a reoperation after an abscess is surgically drained. A reinfection was defined as a persisting or new reddened wound with signs of induration and fluctuation. If there were any signs of purulent exudation with the above-mentioned signs, we considered the wound to be reinfected, and a reoperation was performed. A reoperation was defined as any operation performed in the same region within the time frame of the study control (12 weeks postoperative).

#### Secondary Outcome

Secondary outcomes are measured using specific scar scores as well as nonspecific outcome tools as shown in Table 1.

##### Specific Scar Tools

The Vancouver Scar Scale (VSS) [16], first described by Sullivan in 1990, assesses 4 variables: vascularity, height/thickness, pliability, and pigmentation. These variables are assessed by the surgeon without the perception of the patient concerning his or her scars.

The Patient and Observer Scar Assessment Scale (POSAS) includes subjective symptoms of pain and pruritus of the scar. It consists of 2 numerical scales: the patient scar assessment scale and the observer scar assessment scale. It assesses vascularity, pigmentation, thickness, relief, pliability, and surface area, and it incorporates patient assessments of pain, itching, color, stiffness, thickness, and relief [17].

##### Nonspecific Tools

Health status measurement will be performed using the Short Form Health Survey (SF-36) in all patients. The SF-36 is a 36-item, patient-reported survey of patient health. The questionnaire includes 8 sections (vitality, physical functioning, bodily pain, general health perceptions, physical role functioning, emotional role functioning, social role functioning, and mental health) and in each a score ranges between 0 and 100. The score is proportional to the outcome, with the best possible result of 100 [18,19].

The EQ-5D is a standardized measure of health status developed by the EuroQol Group. The 5-dimension, 5-level questionnaire consists of 2 pages: the EQ-5D descriptive system and the Visual Analog Scale (VAS). The descriptive system comprises 5 dimensions (mobility, self-care, usual activities, pain/discomfort, and anxiety/depression) and each dimension has 5 levels (no problems, slight problems, moderate problems, severe problems, and extreme problems). Additionally, the VAS records the respondent’s self-rated health on a 20 cm vertical visual analog scale with endpoints labeled “the best health you can imagine” and “the worst health you can imagine.”

A self-designed questionnaire was made to investigate the expenditure during the home-care service visits. Questions concerning the time each home-care service person has spent with wound dressing, type of material (gauze, tape, solution, syringes), and amount of time spent are being recorded. In addition, questions concerning time and frequency of family doctor visits and duration of inability to work will be documented.

A medical questionnaire answered by the surgeon in the outpatient clinic documents the size of the wound cavity. Additionally, the surgeon needs to comment on whether there are signs of cellulitis (defined as flushed tissue with signs of induration), the quality of the wound (cavity and edges), any exudation from the wound or signs of persisting fluctuation (liquid-filled cavities).

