Considering a trend toward cost-effective medicine and a reasonable use of medical infrastructure, it is questionable whether every wound needs to be irrigated with a sterile solution twice a day by a special home-care service. We consider the nonsterile wound irrigation (carried out in the shower) as a potential treatment option that offers independence for the patient. It is expected that patients can carry it out independently or with the help of a family member. Additionally, this could lead to an earlier return to work [8].

We hypothesize that simple wound irrigation with nonsterile water for postoperative wound care is feasible after surgical draining of abscesses. Moreover, we postulate that wound irrigation in the shower (simple wound irrigation) is equal to sterile wound irrigation accomplished by special home-care service teams in terms of reinfection and reintervention rates. Additionally, we claim that patients who irrigate the wound using nonsterile water (shower irrigation) will be more independent and that the overall costs are less compared to sterile water irrigation due to less frequent consultations of the home-care services.

To our knowledge, this is the first prospective randomized trial evaluating the value of postoperative wound irrigation using nonsterile solution in surgically drained abscesses.

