### Outpatient Control Visits

All patients receive a standard postoperative outpatient control visit after 1, 3, 6, and 12 weeks. All questionnaires except the VSS and the POSAS will be answered during each visit as shown in Table 1. The VSS and POSAS will be used at the 12-week control visit as definite wound healing is needed to answer these questionnaires. As this is a single-blinded trial, it is essential to ensure blinding of the investigator at the outpatient control visit. All outpatient follow-ups will be carried out by two blinded surgeons investigating the wound and filling out the questionnaire.

**Table 1 table1:** Timeline of outcome measurements.

		Study period					
		Enrollment	Allocation	Outpatient control			
		ED^a^	Operation	Week 1	Week 3	Week 6	Week 12
Enrollment							
	Inclusion criteria	X					
	Informed consent	X					
	Randomization	X					
	Patient baseline characteristics	X					X
Interventions							
	Control group	X	X	X	X	X^b^	X
	Intervention group	X	X	X	X	X^b^	X
Assessments							
	SF-36^c^	X		X	X	X^b^	X
	VAS^d^	X		X	X	X^b^	X
	EQ-5D^e^	X		X	X	X^b^	X
	Medical questionnaire	X		X	X	X^b^	X
	VSS						X
	POSAS						X

^a^Emergency department.

^b^Optional outpatient control, only necessary if wound still open at 3 weeks control.

^c^SF-36: Short Form Health Survey.

^d^VAS: Visual Analog Scale.

^e^EQ-5D: EuroQol 5-Dimension Questionnaire.

^f^VSS: Vancouver Scar Scale.

^g^POSAS: Patient and Observer Scar Assessment Scale.

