### Calculation of Cost Savings

Since nonsterile wound care is easier to perform, we presume that patients in this group are more likely to perform their wound care without the help of a home-care service. Since the dressing in some cases cannot be performed independently and some patients may not have any family member to help, some patients in the nonsterile group may need assistance by a home-care service as well. Also, some patients or family members might feel the need for supervision in the beginning of the wound care, which will be carried out by the home-care service. We assume that on average 1 week of assistance will be enough time and therefore calculated 1 week of home-care service for the nonsterile group.

In contrast, we think that patients in the sterile group are not likely to be able to perform the wound care on their own. Also family members might not be able to provide adequate assistance in sterile wound irrigation and therefore patients are more likely to depend on the home-care service for the entire open wound treatment period. We assume that an average treatment will last 4 weeks.

The estimated time for a proper wound treatment by the home-care service is 20 minutes. Wound treatment is carried out twice per day, totaling 280 minutes each week. The home-care service in the city of Lucerne costs 65 CHF (Swiss Francs) per hour, leading to 305 CHF per week.

If an average treatment lasts 4 weeks and patients from the nonsterile group are thought to be independent after 1 week while patients from the sterile group will need assistance for 4 weeks, a savings of 915 CHF for each patient in the nonsterile group can be assumed solely based on the health care costs. Over the last year, 320 patients with abscesses have been treated at our hospital. Changing our postoperative treatment strategy from a sterile to nonsterile aftercare would save approximately 300,000 CHF annually solely on medical expenses.

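### The cost questionnaire, as described, records dressing material only at home-care visits, so a saving computed from it is biased towards the shower arm (minor; secondary cost claim only)

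*Protocol article*

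**What the plan says.** The Introduction of the protocol article sets out a cost hypothesis for shower irrigation: "the overall costs are less compared to sterile water irrigation due to less frequent consultations of the home-care services".

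Nonspecific Tools describes the instrument that would supply the cost data: "A self-designed questionnaire was made to investigate the expenditure during the home-care service visits". It gives the content as "Questions concerning the time each home-care service person has spent with wound dressing, type of material (gauze, tape, solution, syringes), and amount of time spent", and then adds that "questions concerning time and frequency of family doctor visits and duration of inability to work will be documented". None of the tools described there, and no row of Table 1, is said to cover dressing changes done without home-care.

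Intervention Group (Group II) makes self-care the default in the shower arm: "The patient and/or family members are trained to adequately manage the wound and change the dressings". Home-care is requested only for patients who cannot do the dressing alone. Each change still uses moist gauze, dry nonsterile gauze and tape.

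Calculation of Cost Savings gives the planning figures. Treatment is twice daily for 4 weeks on average. For the shower arm, "We assume that on average 1 week of assistance will be enough time". Control patients are expected to rely on home-care for as long as the wound is open.

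**The concern.** The claim concerns overall cost, but the stated scope of the instrument is cost at home-care visits. How far the two differ depends on the arm. In the control arm nearly every dressing change is expected to be a home-care visit, so its material is recorded. In the shower arm most changes are expected to happen at home without home-care, so their gauze and tape are not recorded. The missing cost therefore follows from allocation and falls mainly on the new strategy.

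A cost comparison computed from this form would show a saving that is partly an artefact of what was recorded. At stake is the size of a secondary cost claim, which the article repeats in its conclusions and discussion as a reason to adopt shower care. The noninferiority comparison is not involved.

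**Working it through.** **Inputs** (Calculation of Cost Savings): 20 minutes per treatment, 2 treatments a day, 65 CHF per home-care hour, 4 weeks of treatment, home-care for 1 week (shower arm) or 4 weeks (control arm), 320 patients a year. The article gives no price for dressing material.

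**The article's own figures.**
- Minutes per week: 20 × 2 × 7 = 280, as stated.
- Cost per week: 280 / 60 × 65 = 303.33 CHF; stated 305.
- Saving per patient: 3 × 305 = 915 CHF, as stated.
- Annual saving: 915 × 320 = 292,800 CHF; stated as approximately 300,000.

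The chain reproduces apart from rounding. It contains home-care labour only, with no material in either arm.

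**Changes without recorded material.**
- Changes per patient: 2 × 7 × 4 = 56.
- Shower arm with home-care: 2 × 7 × 1 = 14.
- Shower arm without home-care: 56 − 14 = 42, and 42 / 56 = 75%.
- Control arm: 0 of 56 if home-care does every change. The article calls this likely, not certain, so few or none.

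**Bias in a questionnaire-based saving.** Let c and s be the material price per change in the control and shower arms.
- Saving with all changes costed: 915 + 56c − 56s.
- Saving from the questionnaire: 915 + 56c − 14s.
- Difference: 42s, always in favour of the shower arm. If k control changes per patient also went unrecorded, the difference would be 42s − kc.

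**Size, with an assumed c = s of 2 to 5 CHF.**
- At 2 CHF: the measured saving is 915 + 112 − 28 = 999 CHF, the full saving is 915, and the excess is 84. 84 / 999 = 8.4%.
- At 5 CHF: the measured saving is 915 + 280 − 70 = 1,125 CHF, the full saving is 915, and the excess is 210. 210 / 1,125 = 18.7%.

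**Sensitivity to the duration of home-care in the shower arm** (same price assumption; labour saving is 305 CHF per week avoided).

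| Home-care weeks | Unrecorded changes | Share of 56 | Labour saving | Excess at 2 / 5 CHF | Measured saving at 2 / 5 CHF | Excess as share |
|---|---|---|---|---|---|---|
| 1 | 42 | 75% | 915 | 84 / 210 | 999 / 1,125 | 8.4% / 18.7% |
| 2 | 28 | 50% | 610 | 56 / 140 | 666 / 750 | 8.4% / 18.7% |
| 3 | 14 | 25% | 305 | 28 / 70 | 333 / 375 | 8.4% / 18.7% |

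The excess in CHF shrinks with longer home-care. Its share of the measured saving does not, because the labour saving shrinks in step.

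**Could the saving reverse?** On 915 + 56c − 56s, the full saving turns negative only if s exceeds c by more than 915 / 56 = 16.3 CHF per change. Nothing in the article suggests that nonsterile material costs more than sterile.

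**The case against.** The strongest objection is that the form itself is not shown. The article summarises it in a few sentences, the ethics committee approved it, and the Results section reports that some shower-arm patients still depend on home-care, so the investigators know something about who does the changes. It stands that nobody can say from the article that no such item exists. But the point does not rest on silence: the article states the scope of the questionnaire and lists its content, and that scope is narrower than the claim.

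Second, the hypothesis attributes the lower cost to fewer home-care consultations, which the form does measure, and the planning section restricts its estimate to health care costs. This stands for unpaid patient or family time, which a payer perspective may set at zero; no such time is counted in the size above. It does not dispose of the gauze and tape, since the hypothesis speaks of overall costs.

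Third, a reader might infer that the 915 CHF figure is itself too high, by 84 / 915 = 9% to 210 / 915 = 23%. The article does not support that. The 915 CHF is labour only, so omitted material is not part of it. If control supplies cost at least as much as shower supplies, the full saving is at least 915 CHF.

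Fourth, the supplies differ: the control arm uses sterile dressings, syringes and Ringer's lactate or saline, and the shower arm uses water and nonsterile dry gauze. Equal prices are therefore only an assumption. A higher control price leaves the excess at 42s but makes it a smaller share of the measured saving.

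A reader might also infer that independence cannot be assessed. The Introduction treats care by the patient or a family member as independent, so absence of home-care is a reasonable measure of it. Skipped irrigation is a separate adherence question. The questionnaire has no row in Table 1 ("Timeline of outcome measurements"), but the text above the table schedules every questionnaire except the two scar scales at each visit, so the missing row is editorial.

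**Conclusion.** The point holds for a cost comparison run on the questionnaire as described. It would omit dressing material mainly in the shower arm and overstate that arm's saving by the number of unrecorded changes times the material price: 84 to 210 CHF per patient, about 8% to 19% of the measured saving.

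The direction rests on the article's own description of the form and of who changes the dressings. The 42 changes rest on its planning assumptions of 4 weeks' treatment and 1 week of home-care in the shower arm, with home-care throughout in the control arm. The prices, and their equality across arms, are assumptions made here.

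This is a bias in a secondary claim. The working does not show that shower care fails to save money, nor that the planning estimate is wrong. Severity is minor; the primary endpoint, sample size and safety are untouched.

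**What to change.** In both arms, have the questionnaire ask at each visit for the number of dressing changes since the last visit, who did them (patient, family, home-care, family doctor) and the materials used, whoever did them. Compute cost from all changes, and report unpaid patient or family time separately as a societal-perspective item. A row for the questionnaire in Table 1 would settle its schedule.

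For patients already followed with the current form, or if the form is not changed, limit the cost claim to home-care expenditure. At publication 50 of the planned 128 patients were enrolled, so a change at that point could still cover the remaining 78 in full.

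The cost is a few lines on an existing form, slightly more patient burden, a form amendment partway through the trial with two versions to handle in the analysis, and probably a less favourable cost difference.

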### Outpatient Control Visits

All patients receive a standard postoperative outpatient control visit after 1, 3, 6, and 12 weeks. All questionnaires except the VSS and the POSAS will be answered during each visit as shown in Table 1. The VSS and POSAS will be used at the 12-week control visit as definite wound healing is needed to answer these questionnaires. As this is a single-blinded trial, it is essential to ensure blinding of the investigator at the outpatient control visit. All outpatient follow-ups will be carried out by two blinded surgeons investigating the wound and filling out the questionnaire.

**Table 1 table1:** Timeline of outcome measurements.

		Study period					
		Enrollment	Allocation	Outpatient control			
		ED^a^	Operation	Week 1	Week 3	Week 6	Week 12
Enrollment							
	Inclusion criteria	X					
	Informed consent	X					
	Randomization	X					
	Patient baseline characteristics	X					X
Interventions							
	Control group	X	X	X	X	X^b^	X
	Intervention group	X	X	X	X	X^b^	X
Assessments							
	SF-36^c^	X		X	X	X^b^	X
	VAS^d^	X		X	X	X^b^	X
	EQ-5D^e^	X		X	X	X^b^	X
	Medical questionnaire	X		X	X	X^b^	X
	VSS						X
	POSAS						X

^a^Emergency department.

^b^Optional outpatient control, only necessary if wound still open at 3 weeks control.

^c^SF-36: Short Form Health Survey.

^d^VAS: Visual Analog Scale.

^e^EQ-5D: EuroQol 5-Dimension Questionnaire.

^f^VSS: Vancouver Scar Scale.

^g^POSAS: Patient and Observer Scar Assessment Scale.

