### Statistical Analysis

Statistical analysis will be performed using SPSS version 21 (IBM Corp). The mean and standard deviation will be calculated and reported for basic patient-related data. Primary analysis will be carried out comparing frequency of reintervention between the intervention and control groups. Moreover, we will try to identify risk factors as basic patient-related data or surgery-associated factors (time of surgery, operation time, experience of the surgeon) using regression models.

Secondary clinical outcome measures will be presented in means with the corresponding standard deviation. The intervention group and the control group will be compared using mean value analysis models (*t* test; multifactorial mean value analysis). We will assume that data missing will be random; therefore, missing data will not be imputed, as we will use the mixed model approach for the longitudinal analyses.

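### VSS and POSAS need a healed wound and are scored once, at week 12, so scores missing because a wound is still open should not be treated as randomly missing (secondary outcomes, minor)

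*Protocol article*

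**What the plan says.** Outpatient Control Visits, on timing: the VSS and POSAS are taken at week 12 because "definite wound healing is needed to answer these questionnaires". Table 1 shows both scales at week 12 and at no other visit. No footnote restricts who is scored. The week-6 visit does carry a condition: "Optional outpatient control, only necessary if wound still open at 3 weeks control".

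Statistical Analysis, on method: "Secondary clinical outcome measures will be presented in means with the corresponding standard deviation". The arms are then compared by *t* test or a multifactorial analysis of means. On missing data: "We will assume that data missing will be random; therefore, missing data will not be imputed". The reason follows in the same sentence: "as we will use the mixed model approach for the longitudinal analyses".

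Primary Outcome counts as a reoperation "any operation performed in the same region within the time frame of the study control (12 weeks postoperative". The failure window therefore ends at the same time as the only scar assessment.

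Calculation of Cost Savings gives the one figure on duration: "We assume that an average treatment will last 4 weeks".

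**The concern.** If a scale can be answered only for a healed wound, a wound still open at week 12 gives no valid score. Whether the score is missing then depends on healing, which is closely related to the primary endpoint and may differ between arms. That is not random missingness in any sense that would justify simply leaving these patients out.

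What remains is a comparison of means among healed wounds, a group formed after randomisation. If nonsterile irrigation left more wounds open at week 12, the worst results would leave that arm and the scar comparison would flatter it. If the sterile arm had more open wounds, the error would run the other way. In a trial that aims to show comparable results, the first case matters more, because it points towards the hoped-for conclusion. What is at stake is what can be said about scars; the noninferiority conclusion on reinfection and reoperation is not involved.

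**Working it through.** **Step 1. Can a wound be open at week 12 under this protocol?** Yes. A reoperation counts up to week 12, and a reinfection may be a persisting one (Primary Outcome). With the assumed average treatment of 4 weeks, and the further assumption that a re-drained wound follows a similar course, a reoperation after about week 12 − 4 = 8 would on average still be open at the scar assessment. A failure well before that would usually have healed and would be scored.

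**Step 2. Does the stated reason for not imputing reach these scales?** A mixed model can tolerate some missing visits because it uses the same patient's other visits. Table 1 gives the SF-36, VAS and EQ-5D repeated visits. It gives the VSS and POSAS one visit and no baseline, so an unscored patient has no other value of that scale to draw on and simply drops out of the mean.

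**Step 3. How many patients?** The documents give no share of wounds unhealed at week 12, so there is no figure of the plan's to reproduce on this point. I take the planned 58 per arm before inflation as given (58 × 1.10 = 63.8, stated as 64); nothing below depends on how 58 was derived. Two figures give a rough sense of scale:

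- Results reports 2 reoperations among 50 enrolled: 2/50 = 4%, and 0.04 × 58 = 2.3 per arm. This pools the arms, follow-up was incomplete, it misses wounds that healed slowly without reoperation, and it does not say whether the two wounds were open at week 12.
- Sample Size Calculation names a 15% reinfection rate: 0.15 × 58 = 8.7 per arm. This would apply only if 15% is an event rate, which the section leaves unclear, and if every reinfected wound were still open at week 12.

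**Step 4. How large is the effect on the scar comparison?** Let u be the share unhealed in an arm and D the number of SDs by which unhealed wounds would score worse than healed ones. With the same mean m for healed wounds in both arms, the mean over all patients in an arm is (1 − u)m + u(m + D) = m + uD. The arm difference over all patients is D × (u_intervention − u_control), while the healed-only comparison shows 0. The hidden difference is therefore D × (u_intervention − u_control). All values of u and D here are assumptions.

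| Unhealed, control v intervention | Unscored of 58, control v intervention | Hidden difference, D = 1 to 2 |
|---|---|---|
| 0% v 0% | 0 v 0 | 0 |
| 5% v 5% | 2.9 v 2.9 | 0 |
| 5% v 10% | 2.9 v 5.8 | 0.05 to 0.10 SD |
| 5% v 15% | 2.9 v 8.7 | 0.10 to 0.20 SD |

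For scale, the standard error of a difference in means with 58 per arm is √(2/58) = 0.19 SD. The 5% v 10% case is about half a standard error or less.

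**The case against.** The strongest reply is that the healing phrase explains why week 12 was chosen and is not an exclusion rule. Table 1 puts no restriction on the two scales, although it does footnote the conditional week-6 visit, and no sentence says unhealed patients are left out. That is a fair reading, and it means the exclusion is inferred. It does not remove the problem: if every patient is scored regardless, the scales are applied to wounds that the protocol itself says cannot answer them.

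Second, the missing-data sentence is tied to the longitudinal analyses, so applying it to single-visit scales is an extension. This also stands. The article does not claim that a mixed model will rescue the scar scores. It is, however, the only missing-data rule given and it is worded generally, so its scope should be stated.

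Third, scar quality is undefined without a scar, so any difference that includes open wounds rests on an imposed score, and a worst rank partly counts the primary endpoint again. A healed-only comparison read beside the primary endpoint is defensible. I accept this; it is why the worst-rank analysis is proposed only as a sensitivity analysis.

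Fourth, the handling of unscorable patients may be left to an analysis plan that is not shown. The lack of such a rule is therefore not the point. The point is that the general assumption that is printed does not suit these two scales.

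**Conclusion.** The point stands in a narrow form. Wounds not healed at week 12 cannot validly be scored on the VSS or POSAS, their absence depends on outcome, and the random-missing assumption with its mixed-model reason should not be applied to these scales. The size is unknown and may be small. It is nil if all wounds heal or if the unhealed shares are equal, and 0.05 to 0.10 SD in the 5% v 10% illustration, which rests on assumed shares, an assumed deficit of 1 to 2 SD and equal healed-wound means.

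A reader might infer more than the documents support:

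- *That failed wounds in general drop out of the scar comparison.* They do not. An early reinfection or reoperation that heals by week 12 is scored, and its scar stays in.
- *That about 9 of 58 per arm would be unscored.* The 15% is a reinfection figure of unclear role, not a share unhealed at week 12.
- *That the scar result is biased towards nonsterile care.* This would need more unhealed wounds in that arm, and nothing in the documents shows it.

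Only secondary outcomes are affected, and the severity is minor.

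**What to change.** 1. Restrict the random-missing, no-imputation statement to the longitudinal questionnaires (SF-36, VAS, EQ-5D).
2. Report the number and proportion of wounds healed at week 12 by arm beside the scar scores. The surgeon's medical questionnaire already records cavity size, wound quality, exudation and fluctuation at that visit. State which entries count as healed, and count patients lost to follow-up separately from patients seen with an open wound.
3. Label the VSS and POSAS comparison of means as conditional on healing.
4. Add a rank-based sensitivity analysis in which unhealed wounds receive the worst rank.

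No new data collection is needed. The cost is some wording, one extra analysis whose result is on a rank scale instead of a mean difference, and a more cautious conclusion about scars.

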**Methods:**

In a prospective, randomized controlled, single-blinded, single-center trial based on a noninferiority design, we will enroll 128 patients randomized to either the control or the intervention group. The control group will be treated according to our current, standard protocol in which all patients receive a sterile wound irrigation performed by a home-care service twice a day. Patients randomized to the intervention group will be treated with a nonsterile wound irrigation (shower) twice a day. All patients will have a routine clinical control visit after 1, 3, 6, and 12 weeks in the outpatient clinic. Primary outcome is the reinfection and reoperation rate due to insufficient wound healing diagnosed either at the outpatient control visit or during general practitioner visits. Secondary outcome measures include a Short Form Health Survey, Visual Analog Scale, Patient and Observer Scar Assessment Scale, Vancouver Scar Scale, and the EurolQol 5-Dimension Questionnaire. Those questionnaires will be completed at the outpatient control visits.

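### The week-6 visit is for all patients in the text but only for wounds open at week 3 in Table 1; if the table is followed, week-6 data are selected on a post-randomisation outcome

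*Protocol article*

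**What the plan says.** The Protocol article gives two schedules for week 6.

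- **Text, Outpatient Control Visits:** "All patients receive a standard postoperative outpatient control visit after 1, 3, 6, and 12 weeks".
- **Abstract, Methods:** "All patients will have a routine clinical control visit after 1, 3, 6, and 12 weeks in the outpatient clinic".
- **Table 1, footnote b:** "Optional outpatient control, only necessary if wound still open at 3 weeks control". In the week-6 column the footnote is attached to both group rows and to the SF-36, VAS, EQ-5D and medical questionnaire.

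The surrounding provisions that matter are these:

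- Questionnaires: "All questionnaires except the VSS and the POSAS will be answered during each visit as shown in Table 1".
- Blinding: "All outpatient follow-ups will be carried out by two blinded surgeons investigating the wound and filling out the questionnaire".
- Primary endpoint: "We defined the primary endpoint as a reinfection or a reoperation after an abscess is surgically drained". The abstract adds that events may be "diagnosed either at the outpatient control visit or during general practitioner visits".
- Missing data (Statistical Analysis): "We will assume that data missing will be random". Nothing is imputed, and a mixed model is named for the longitudinal analyses. Secondary outcomes are also to be given as means with SD and compared by t test and multifactorial models, with no time point stated. That section mentions neither the conditional visit nor wound status at week 3.

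**The concern.** Whether a wound is still open at week 3 is known only after randomisation, and the aftercare under test could affect it. If that state decides who is measured at week 6, the week-6 groups are no longer the randomised groups. A real benefit of faster healing could vanish from the observed means, or a difference could appear where none exists.

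The footnote also covers the medical questionnaire, on which the blinded surgeon records induration, exudation and fluctuation. These are the signs that the protocol uses to define reinfection. Under the footnote, the number of blinded checks a patient receives depends on how fast the wound healed.

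**Working it through.** No stated figure is in dispute, so the check sets the passages side by side and then works through what follows if the footnote is applied.

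**1. Can both rules hold?** The text and the abstract include week 6 for every patient. The footnote requires it only for a wound open at week 3. For a patient healed at week 3 they give different answers, so both cannot hold.

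**2. Blinded checks.** Study visits are at weeks 1, 3, 6 and 12 and the endpoint window is 12 weeks.
- Week 6 attended: gaps after week 3 are 6 − 3 = 3 weeks and 12 − 6 = 6 weeks.
- Week 6 omitted: one gap of 12 − 3 = 9 weeks.

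The loss is one blinded check.

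**3. Number measured at week 6.** The protocol gives 58 per arm before the allowance for loss, but no week-3 open rate. Assuming rates from 30% to 70%, the number with required week-6 data runs from 58 × 0.30 = 17.4 to 58 × 0.70 = 40.6 per arm, or about 17 to 41.

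**4. A true difference can be hidden (assumed values).** Let the week-6 score average 80 if healed at week 3 and 60 if open, in both arms, with 40% open in arm A and 60% in arm B.
- All patients: A = 0.6 × 80 + 0.4 × 60 = 72; B = 0.4 × 80 + 0.6 × 60 = 68; difference 4.
- Open wounds only: 60 − 60 = 0.
- All patients, with week-3 status as a covariate: within each status the arms are equal, so the adjusted arm difference is again 0.

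Covariate adjustment therefore does not recover the 4 points. Averaging over status within each arm does (72 v 68), but it needs a week-6 mean for healed patients.

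**5. A false difference can appear (assumed values).** Let a latent healing tendency *u* be standard normal. The week-6 score is 70 + 8*u* + noise of SD 15, with no true arm difference. A wound is open at week 3 when 0.6*u* + 0.8*e* falls below z_p, where *e* is independent standard normal and *p* is the open rate. The mean score among open wounds is then 70 − 8 × 0.6 × φ(z_p)/p:

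| Open rate p | φ(z_p)/p | Mean among open |
|---|---|---|
| 0.3 | 1.159 | 64.4 |
| 0.4 | 0.966 | 65.4 |
| 0.5 | 0.798 | 66.2 |
| 0.6 | 0.644 | 66.9 |

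The artefact, taken as the arm with more open wounds minus the other arm, is:
- 50% v 50%: 0
- 50% v 60%: 4.8 × (0.798 − 0.644) = 0.7
- 40% v 60%: 4.8 × (0.966 − 0.644) = 1.5
- 30% v 60%: 4.8 × (1.159 − 0.644) = 2.5

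Simulating the same model gave −0.02, 0.73, 1.59 and 2.49. The all-patient difference was about 0 throughout.

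Steps 4 and 5 err in different ways, so not even the direction of the bias can be fixed from the document.

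**The case against.** The strongest reply is that this is a table slip affecting one secondary time point. Much of that stands.

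- **Missing data.** A reader might infer that the footnote makes the missing-at-random assumption false. The document does not support that. Week-3 wound state is recorded on the medical questionnaire, and omission driven by a recorded variable can be missing at random. The mixed model would also use each patient's scores from weeks 1, 3 and 12. What remains is that the Statistical Analysis section does not say wound status is used.
- **Week-6 t test.** None is named. A t test is planned for secondary outcomes without a time point, so the criticism applies only if such a comparison is made or if raw week-6 means are read as comparative.
- **Primary endpoint.** A reader might infer that reinfections after week 3 in healed patients would be found only through unblinded care. That goes too far. Week 12 applies to everyone and is blinded, so a reinfection still present then is seen. General practitioner diagnoses count under either schedule. The stated primary analysis compares reinterventions, and reoperations count throughout the 12 weeks. The exposed events are reinfections that arise and resolve between visits.
- **Exclusion criterion.** Excluding patients who cannot return at week 6 requires availability only. It is compatible with a conditional visit and does not settle the conflict.
- **Reference to Table 1.** The sentence on questionnaires refers to the table, so the footnote might be read as qualifying it. The sentence on visits and the abstract carry no such qualification.
- **Size.** The illustrations rest on assumed values. The cost section assumes an average treatment of 4 weeks, which suggests, but does not prove, that many wounds are open at week 3. More open wounds would mean fewer missing week-6 data. Similar open rates in the two arms could make the bias small.

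None of this removes the contradiction or the selection that follows from the footnote.

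**Conclusion.** The contradiction is explicit and certain. Its consequences depend on which rule is followed. Under the footnote, observed week-6 SF-36, VAS, EQ-5D and wound data describe only patients selected on healing after randomisation, and an unadjusted week-6 comparison is not a randomised one. Patients healed at week 3 lose one blinded check.

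The effect on the primary endpoint is limited, and the week-1, week-3 and week-12 assessments are not affected by the footnote. The bias at week 6 cannot be sized or signed without week-3 open rates by arm. The figures above (4 points hidden, or 0 to about 2.5 points created) show what is possible under stated assumptions and are not estimates for this trial. The point deserves correction because correction is cheap and, with 50 of 128 patients enrolled at publication, still useful. It does not threaten the main conclusion.

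**What to change.** **Reconcile the table with the text.** State that the week-6 study assessments (SF-36, VAS, EQ-5D and the blinded medical questionnaire) are collected from all patients, as the text and abstract already say. This concerns data collection only; it does not judge when a clinical control is needed. The cost is a table correction and some extra clinic time compared with practice under the footnote.

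**For patients already followed under the footnote:**
- Make no unadjusted between-arm comparison at week 6, and label any raw week-6 means as covering patients with open wounds.
- Use week-3 wound status only as an auxiliary variable, for example in multiple imputation by arm or by averaging over status within arm. Do not enter it as a covariate that adjusts the treatment effect.
- Report the week-3 open rate by arm, so that the extent of selection can be seen.

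One limit should be stated with the results. If no healed patient has week-6 data, the imputation rests on scores from other visits and on the model. Collecting week 6 from everyone from now on, up to 128 − 50 = 78 further patients, would supply observed week-6 scores in healed patients to support it. The analytic part costs only a few lines in the analysis plan.
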